# Study protocol for a randomized controlled trial comparing pulse pressure variation (PPV) and central venous pressure (CVP) guidance for fluid responsiveness assessment in neurosurgical patients undergoing posterior fossa tumor resection in park bench position

**DOI:** 10.1371/journal.pone.0324590

**Published:** 2025-06-02

## Abstract

**Introduction:**

Suboccipital craniotomy in the park bench position is linked to considerable physiological alterations. Effective fluid management in this context is a challenge to anesthesiologists. No published data exist on pulse pressure variation and central venous pressure guidance in patients undergoing tumor resection in the park bench posture. We undertake a study to evaluate the concept that two approaches of goal-directed fluid treatment enhance optimal fluid management and improve hemodynamic stability. We established the fluid management protocol for this process.

**Methods and analysis:**

This is a prospective randomized double-blinded study of adult patients undergoing suboccipital craniotomy to remove tumors in the park bench position. The comparison of pulse pressure variation and central venous pressure for fluid management regarding mean intraoperative fluid administration as the primary outcome. A sample size of 54 will yield over 80% power to identify a mean fluid difference of at least 500 ml between two specified methods. The secondary outcomes are data pertinent to fluid administered during and after surgery, including the lowest systolic blood pressure, serum lactate levels, vasopressor utilization, and duration of ICU stay. The statistical analysis will be validated based on the data distribution and types of data. This is the first study to examine two goal-directed fluid therapies, pulse pressure variation and central venous pressure, in patients with posterior fossa tumors and undergoing surgery in the park bench position. Researchers want to contribute novel information to the domain of fluid optimization in neurosurgery.

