### Randomization and blinding

The schedule of enrolment, interventions, and assessments is shown in Fig 1. Patients will be randomly allocated to either CVP (group 1) or PPV (group 2)-guided fluid administration in a 1:1 ratio (Fig 2). Block randomization of block sizes 4, 6, and 8 was used to guarantee that the patient would be randomly and uniformly assigned to each group. A unique randomization code was generated from the website (sealedenvelope.com) by an independent research assistant [19]. The randomized code is sealed in an opaque envelope and will be opened when the patient arrives in the operating room.

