### Sample size calculation

The primary outcome is the intraoperative fluid volume administered. The calculation of sample size utilized data from the research conducted by Janani Gopal et al [18]. The average fluid volume administration of patients in the CVP and PPV groups were 4,300 and 3,500 ml, respectively. In another study, the groups that used CVP guidance and those that used PPV guidance had a mean intraoperative fluid volume difference of 556 milliliters [25]. With the power of 80%, a 0.05 two-sided difference, the calculated sample size was 25 patients/group. Given a dropout rate of 5%, we will enroll 54 patients. The website clincalc.com is used to calculate the sample size. We anticipate a minimal drop-out and low loss to follow-up rate, as the study is conducted while the patient is under general anesthetic during surgery. Additionally, post-surgery, all patients will be admitted to the neurosurgical ICU, where we can gather data regarding the duration of their ICU stay.

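### The abstract's over-80% power for a 500 ml difference does not match the sample-size section, which cites only 800 ml and 556 ml and gives no design difference or SD

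*Protocol article*

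**What the plan says.** The abstract (Methods and analysis) makes a definite power statement for the primary outcome: "A sample size of 54 will yield over 80% power to identify a mean fluid difference of at least 500 ml".

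Sample size calculation, in the body of the article, is where the 54 is derived. It says the calculation drew on data from a cited trial: "The average fluid volume administration of patients in the CVP and PPV groups were 4,300 and 3,500 ml, respectively". It then adds a second study in which CVP-guided and PPV-guided groups "had a mean intraoperative fluid volume difference of 556 milliliters". The result follows: "With the power of 80%, a 0.05 two-sided difference, the calculated sample size was 25 patients/group". The last step is "Given a dropout rate of 5%, we will enroll 54 patients". Allocation is 1:1 (Randomization and blinding), so 54 enrolled means 27 per group.

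The section does not mention 500 ml, does not say which difference was entered, and gives no SD.

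**The concern.** The same 54 patients are tied to one difference in the abstract and to two other, larger differences in the section that should support it. For a fixed sample size, power falls as the difference gets smaller. A size that gives 80% power at 556 ml or 800 ml gives less at 500 ml. The only slack is the dropout allowance.

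Intraoperative fluid volume is the primary outcome, and many readers will take the trial's sensitivity from the abstract. If the over-80% figure at 500 ml is not what the calculation supports, a non-significant result could be read as stronger evidence against a 500 ml difference than it is.

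**Working it through.** **Inputs from the article:** two-sided alpha 0.05, power 80%, 25 per group, 5% dropout, 54 enrolled at 1:1, cited differences of 4,300 − 3,500 = 800 ml and 556 ml, and the abstract's 500 ml. **Not given:** the SD and the design difference.

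**1. The dropout step reproduces.** 25 / 0.95 = 26.3, rounded up to 27 per group, 54 in total. The 25 per group cannot be reproduced without an SD.

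**2. Scaling, which needs no SD.** For two means at fixed alpha and power, n per group = 2 × (1.960 + 0.842)² × (SD/difference)², so n is proportional to 1/difference².

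- From 556 ml to 500 ml: (556/500)² = 1.24, and 25 × 1.24 ≈ 31 per group.
- From 800 ml to 500 ml: (800/500)² = 2.56, and 25 × 2.56 = 64 per group.
- Margin from enrolling 27 rather than 25: 27/25 = 1.08.

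The margin of 1.08 is smaller than either factor. If 556 ml or 800 ml produced the 25, then 27 per group does not reach 80% power at 500 ml, whatever the SD. With all 54 analysed, the difference detectable with 80% power would be 556 × √(25/27) ≈ 535 ml or 800 × √(25/27) ≈ 770 ml.

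**3. SD implied by 25 per group at 80% power.** SD = difference × √(25/2) / 2.802. This gives the upper end of each range below; solving with the noncentral t gives the lower end.

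**4. Power at 500 ml.** The normal approximation is Φ(500 / (SD × √(2/n)) − 1.96). For example, with n = 27 and SD 702 ml, the standard error is 702 × 0.272 = 191 ml, 500/191 = 2.62, and Φ(0.66) ≈ 74.5%. The ranges cover the normal and noncentral t calculations.

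| Assumed design difference | Implied SD (ml) | Power at 500 ml, 25 per group | Power at 500 ml, 27 per group |
|---|---|---|---|
| 800 ml | 989-1010 | 40-43% | 43-46% |
| 556 ml | 688-702 | 69-73% | 73-76% |
| 500 ml | 618-631 | 78-82% | 82-84% |

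**5. Largest SD for which the abstract holds.** Solving for 80% power at 500 ml gives an SD of at most 644 ml (noncentral t) to 656 ml (normal) with 27 per group, and 618 to 631 ml with 25 per group.

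**The case against.** The best reply is that 800 ml and 556 ml are results of earlier studies, cited as background, and that 500 ml was chosen as a minimum difference somewhat below the smaller of them. With an SD of about 618-631 ml, that design gives 25 per group, and enrolling 54 then gives about 82-84% power, which fits the abstract. The documents do not exclude this reading, and the section never says that 800 ml or 556 ml was the difference entered.

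This part of the reply stands. A reader might infer that the trial has only 43-46% or 73-76% power at 500 ml, or that the sample-size arithmetic is wrong. The documents support neither as fact, because the SDs behind those percentages are back-solved under an assumed basis.

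Two further points also stand. The primary outcome is to be reported with a 95% confidence interval, so a null result can be judged from that interval and not only from the planned power. The planned primary analysis is a covariate-adjusted mixed model, so two-sample power is only an approximation to its power.

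The reply does not remove the mismatch. The section says its calculation used data from the study with the 800 ml difference, offers 556 ml as the only other figure, and leaves 500 ml out. The difficulty is not merely a detail left to a fuller document: the article publishes a specific power claim and, for the same 54 patients, a basis that does not show it.

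**Conclusion.** The abstract and the sample-size section do not match, and over 80% power at 500 ml is unsupported as written. If the 25 per group came from either cited difference, the abstract's claim is wrong for any SD: 500 ml would need about 31 or 64 per group, and 54 patients would give about 73-76% or 43-46% power. If it came from 500 ml with an SD of about 618-631 ml, the abstract is right and the section omits its own basis. The article does not allow a choice between these.

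The percentages assume a two-sample comparison of means at two-sided 0.05, equal groups, and exactly 80% power at 25 per group. The failure to reach 80% at 500 ml on a 556 ml or 800 ml basis rests on the scaling alone and needs no assumed SD.

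**What to change.** In Sample size calculation, state the single design difference and the SD that produced 25 per group, and make the abstract agree.

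- **If the basis was 800 ml or 556 ml:** replace the 500 ml sentence in the abstract with that difference and its SD, and report the lower power at 500 ml.
- **If the basis was 500 ml:** say so in the section, give the SD and its source, and present 800 ml and 556 ml as background only.

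This is a change of wording and needs no additional patients. The only cost is that the stated power or detectable difference may look less favourable.

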**Trial registration:**

ClinicalTrials.gov NCT06595667.

## Introduction

Fluid management plays an important role in the perioperative care of neurosurgical patients, particularly those undergoing posterior fossa tumor resection [1,2]. In these procedures, patients are often placed in the park bench position [3,4]. The park bench position is a lateral positioning technique in which the head is oriented toward the surgical side, while the arm on the contralateral side of the lesion dangles off the operating table. The park bench position facilitates surgeons’ access to pathology in the parietal, temporal region, and cerebellar-pontine angle (CPA) [5]. Surgery in the park bench position induces various physiological alterations, including oxygenation-ventilation matching, and hemodynamics [3,5]. Evaluating the sufficiency of fluid replacement during surgery is difficult while the patient is in the park bench position. The accumulation of blood in the dependent part, inferior vena cava (IVC) compression, positive intrathoracic pressure, and decreased peripheral vascular resistance affect the accuracy of fluid replacement evaluation [4,5]. Additionally, surgery in the posterior fossa, which houses the brainstem, leads to hemodynamic fluctuations and complicates the interpretation of fluid responsiveness and volume replacement [6,7].

Intraoperative fluid management is crucial to avert problems such as cerebral hypoperfusion or brain edema, which can significantly impact patient outcomes [1]. Multiple methods, static and dynamic indices, have been used to guide fluid administration intraoperatively [8]. Two methods that are frequently employed are central venous pressure (CVP) guidance and pulse pressure variation (PPV) guidance [9–11]. PPV, derived from arterial pressure waveform analysis, reflects the dynamic changes in stroke volume induced by mechanical ventilation, offering a real-time assessment of fluid responsiveness and has been proposed as a reliable indicator of fluid responsiveness in various surgical settings [9]. CVP is the most frequently used preload index [12,13]. The reliability of using CVP values to guide fluid administration should be applied to patients with normal cardiac function. Otherwise, a trend of increasing CVP values during fluid loading does not consistently suggest an increase in cardiac output [12]. Previous studies have revealed that CVP possesses a comparatively low predictive value for fluid responsiveness [13,14]. However, extreme CVP values, specifically below 6 mmHg or beyond 15 mmHg, can provide information about how to modify fluid delivery during surgery [15].

Previous studies indicated that using PPV guidance for fluid management during craniotomy was more reliable than using CVP guidance [16–18]. Nevertheless, such investigations were carried out on supine patients undergoing brain surgery. The reliability of PPV-guided fluid management in those studies was shown by increased hemodynamic stability, decreased incidence of hypotension, and decreased intraoperative fluid requirement, compared to the CVP group [16–18]. As of now, no comparative analysis has been conducted on PPV and CVP concerning fluid management in the park bench position. We developed a prospective, randomized, controlled trial aimed at comparing the fluid management strategies guided by PPV and CVP in patients undergoing sub-occipital craniotomy (SOC) in the park bench position.

## Methods and analysis

The study aimed to investigate whether there are significant differences in fluid responsiveness when using PPV compared to CVP guidance during posterior fossa tumor resection in adult neurosurgical patients positioned in the park bench setup. This study is conducted in compliance with the SPIRIT (Standard Protocol Items: Recommendations for Interventional Trials) guideline.

### Ethical considerations

This study protocol has been approved by the Institutional Ethical Committee of the Faculty of Medicine, Chiang Mai University (CMU), with the protocol number ANE-2567-0391. All participants must provide consent to engage in the study once the research team thoroughly elucidates the study methodology. The results of this study will be published in a peer-review journal. Participants involved in the research may directly request the study results from the researchers upon publication. No additional blood work is required beyond the standard practice for patients undergoing SOC to remove tumors. Participants will be monitored in accordance with established standards of anesthesia care and treated in compliance with the Declaration of Helsinki. Confidential information will be securely stored throughout the duration of the study and thereafter. Participants and their relatives will be provided with a comprehensive overview of the study protocol during the informed consent process. Individuals possess the right to decline participation without experiencing any adverse consequences regarding their treatment and standard of care.

The risk assessment generally encompasses the subsequent factors: 1. Surgical and Anesthetic Risks: Participants in this study will undergo posterior fossa tumor resection in the park bench position, which carries inherent surgical and anesthetic risks, including potential vascular injury, nerve injury, brain edema, respiratory complications, and hemodynamic instability. The procedures utilized in this research do not present additional risks beyond those typically associated with such surgeries. 2. Specific Risks Related to Research: The primary research intervention entails continuous hemodynamic monitoring through the use of central venous pressure (CVP) and pulse pressure variation (PPV). Complications associated with central venous and arterial catheters may arise during insertion or usage. These include pneumothorax, cardiac arrhythmias, arterial injury, infectious complications, and thrombotic complications. Preventing complications requires strict adherence to aseptic techniques during catheter insertion, appropriate site selection, utilization of ultrasound guidance to mitigate mechanical complications, and consistent monitoring of the catheter site.

### Patient and public involvement

There will be no healthy volunteers in this study. The inclusion criteria are (1) adult patients, aged 20–65 years, (2) diagnosis of posterior fossa tumor, (3) scheduled for SOC to remove tumor in the park bench position, and (4) the patient is willing to participate in the study. The day before the procedure, the anesthesiologist will evaluate the patient in the ward, clarify the study protocol, and obtain informed consent. The patients will be notified that they may withdraw from the study at any time without affecting the standard treatment they are entitled to receive. Patients participating in the study will be treated following the standards of the Declaration of Helsinki. Patients with active cardiac illness, arrhythmias, sepsis, vasoactive drug dependence, chronic obstructive airway disease, pulmonary hypertension, and the American Society of Anesthesiologists (ASA) status equal to or greater than III will be excluded. The anticipated duration of participant involvement is one-week following admission to the neurosurgical intensive care unit (ICU) after posterior fossa tumor excision.

### Research site and anticipated schedule

This research is a prospective, single-center, double-blind randomized trial performed at a tertiary care university hospital in Northern Thailand. The institutional ethics committee approved the study protocol from September 26, 2024, until September 25, 2025.The research team intends to prospectively gather patient data from December 1, 2024, to May 31, 2025, in the brain and spinal cord operating room at Maharaj Nakorn Chiang Mai Hospital, as well as postoperative data from the neurosurgical intensive care unit. Data gathering will conclude by June 2025, with outcome analysis expected to be finalized by December 2025. Should the research team determine, within 45 days prior to the expiration of the ethical committee approval date, that recruitment of the planned patient cohort may be unfeasible, we will submit a request for a 6-month extension of the research approval.

### Confidentiality

Patient information, such as names and hospital numbers, will be retained by the co-investigator, while patients will be deidentified and assigned a unique research identification number instead. The publication will not disclose the patient’s identity; however, if required for the patient’s safety, identifying information may be revealed.

### Randomization and blinding

The schedule of enrolment, interventions, and assessments is shown in Fig 1. Patients will be randomly allocated to either CVP (group 1) or PPV (group 2)-guided fluid administration in a 1:1 ratio (Fig 2). Block randomization of block sizes 4, 6, and 8 was used to guarantee that the patient would be randomly and uniformly assigned to each group. A unique randomization code was generated from the website (sealedenvelope.com) by an independent research assistant [19]. The randomized code is sealed in an opaque envelope and will be opened when the patient arrives in the operating room.

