**Fig 2 pone.0324590.g002:**
[figure not shown]
The Consolidated Standards of Reporting Trials flow diagram.

The patients will be blinded to the group allocation as they are under general anesthesia. Surgeons will not be aware of the specifics of the fluid replacement throughout the procedure, even if they can see what the anesthesiologist is monitoring. The anesthesiologists responsible for the patient cannot be blinded as they have to provide fluids according to the study protocol. The statistician analyzing the outcomes will be unaware of the group to which the data pertains.

In the event of a critical occurrence during surgery, such as cardiac arrest or significant arrhythmias resulting in hemodynamic instability, the anesthesiologist will promptly notify the surgeon and disclose the patient allocation group.

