### Anesthesia protocol

At the operation theater, the patients will receive standard ASA monitoring including electrocardiogram (ECG), pulse oximetry (SpO_2_), non-invasive blood pressure, temperature, end-tidal CO_2_ (etCO_2_), Bi-Spectral index (BIS), direct arterial pressure, and central venous pressure (CVP). Two large-bore peripheral venous lines will be established. All patients will have general anesthesia with endotracheal intubation. The target control infusion (TCI), Schnider model, will be used for the total intravenous anesthesia (TIVA) technique. The effect-site concentration of propofol will be started at 6–8 μg.ml^−1^. Tracheal intubation will be facilitated with cis-atracurium 0.2 mg.kg^−1^ and then maintenance infusion dose at 2 μg.kg^−1^.min^−1^ throughout the procedure. Cisatracurium is only used for intubation and not for infusion in certain cases where surgeons need to monitor cranial nerves, such as tumor resection in the CPA region, since it could interfere with the assessment of motor function of those cranial nerves. A mixture of oxygen and air will be used during anesthetization. The patients will receive an intermittent bolus dose of fentanyl, 2–3 μg.kg^−1^. Post-induction, a 20-G arterial catheter will be placed into the radial artery of the arm corresponding to the side of the lesion, which will be positioned on top when the patient is arranged in the park bench position. A 7-Fr, triple-lumen central venous catheter will be inserted in the right subclavian vein, under ultrasound guidance, for the CVP monitoring. Plain bupivacaine 0.5%, 10 ml, will be injected over the nerves supplying the scalp on the surgical side, including the pre-auricular nerve and the greater and lesser occipital nerves. The anesthesiologist will provide 2 ml of 2% lidocaine at each of the three pre-marked locations, five minutes before the surgeon applies the Mayfield head holder. The neuro-surgical resident will insert a urinary catheter. The patient will be carefully positioned on the park bench. The endotracheal tube, intravenous line, arterial line, and CVP line will be re-checked after the position is finalized. The ventilator setting (Maquet Critical Care AB, Sweden) is tidal volume 8 ml.kg^-1^(ideal body weight), respiratory rate will be adjusted to keep normocarbia (etCO_2_ 35–40 mmHg), inspiration: expiration ratio 1:2, positive end-expiratory pressure (PEEP) 5 cmH_2_O, and a fraction of inspired oxygen of 0.5 with air mixture. The intraoperative parameters including heart rate, arterial blood pressure, PPV, and CVP, will be recorded on the Mindray, BeneVision N12 (Shenzhen Mindray Bio-Medical Electronics). The anesthetic depth will be monitored using a BIS monitor (Covidien Ireland Limited) and maintained between 40–60 throughout the operation. Serum blood lactate levels will be evaluated hourly using arterial blood gas analysis throughout the surgical procedure. Mannitol is not routinely given to every patient; it depends on the surgeon’s decision. During the surgery, the patient will receive fluids following the fluid management protocol, contingent upon their classification into the PPV or CVP fluid guidance group. At the end of the surgery, should the patient receive muscle relaxants, they will be antagonized with neostigmine at 0.05 mg. kg-1 and glycopyrrolate at 0.01 mg.kg^-1^. The patient must meet the safe extubation criteria; otherwise, if the surgeon determines that extubation is premature, the patient will stay intubated state and be transferred to the neuro-ICU. The surgeon will be asked to rate the brain relaxation, using a four-point scale (1 = relax, 2 = satisfy, 3 = firm, 4 = bulging) [20]. At the ICU, the anesthesiologist will examine the conjunctival edema, peri-orbital swelling, and the cuff leakage test, if the patient is in the intubated state.

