
### Fluid management protocol

CVP and PPV will be measured and recorded in both groups. Both parameters appear on the monitor screen throughout the operation. As a maintenance fluid, each patient will receive a weight-based formula of 0.9% normal saline solution and lactated Ringer solution [21]. Fluid management protocol will be activated, based on their assigned group (CVP or PPV), as shown in Fig 3. The treatment goal for the PPV group is a PPV value of less than 13%, whereas the treatment goal for the CVP group is a CVP value between 8–12 mmHg [22,23]. Before the implementation of the fluid management protocol, acute blood loss exceeding the permissible threshold and/ or hemoglobin < 9 gm/dl must be addressed and treated with pack red cell (PRC) transfusion [24]. The maximum allowable blood loss (MABL) is determined by considering gender, weight-based estimated blood volume, preoperative hematocrit, and the minimum acceptable hematocrit for the patient.

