### Statistical analysis

Baseline variables will be summarized using descriptive statistics (mean, standard deviation, median, interquartile range, or frequency and percentage, as appropriate). A modified intention-to-treat (ITT) principle will be used for all analyses. Data distribution will be assessed using the Kolmogorov-Smirnov test. Comparisons between groups (PPV vs. CVP) will be conducted as follows:

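### The allocation envelope is opened on arrival in theatre, earlier than any step needs it, so the unblinded anesthesiologist manages the whole set-up knowing the arm

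*Protocol article*

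**What the plan says.** All references are to the protocol article.

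- **Timing of the reveal** (Randomization and blinding): "The randomized code is sealed in an opaque envelope and will be opened when the patient arrives in the operating room".
- **Who knows the arm** (same section, text after Fig 2): "The anesthesiologists responsible for the patient cannot be blinded as they have to provide fluids according to the study protocol". The same paragraph rests patient blinding on the patient being under general anesthesia.
- **Set-up** (Anesthesia protocol): "Post-induction, a 20-G arterial catheter will be placed into the radial artery", and then "A 7-Fr, triple-lumen central venous catheter will be inserted in the right subclavian vein, under ultrasound guidance, for the CVP monitoring". Positioning follows, after which the lines are checked again.
- **When the arm matters** (Anesthesia protocol): "During the surgery, the patient will receive fluids following the fluid management protocol, contingent upon their classification into the PPV or CVP fluid guidance group". The Fluid management protocol section adds: "Fluid management protocol will be activated, based on their assigned group (CVP or PPV), as shown in Fig 3".
- **Monitoring in both arms** (Fluid management protocol): "CVP and PPV will be measured and recorded in both groups".
- **Primary outcome** (Outcomes): mean intravenous volume given intraoperatively, with no start point in the text. The Statistical analysis section models volume at t2 to t5, which the text does not define.
- **Analysis set** (Statistical analysis): "A modified intention-to-treat (ITT) principle will be used for all analyses".

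**The concern.** In an open-label comparison of two fluid rules, the person giving fluid must know the arm once the rules diverge. Before that, the knowledge serves no purpose and can only do harm. Here the outcome is the volume that this same person gives, so any avoidable period of unblinded discretion bears directly on the primary endpoint.

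Two routes are open. First, fluid given around induction, line placement and positioning could differ by arm for reasons unrelated to the guidance rule. It could be counted as intraoperative volume. If it is not counted, it could still shift the first CVP and PPV readings, which then drive protocol fluid. Second, a failed line, a catheter complication or a change of position becomes an event after allocation is known. With a later opening, the same event would precede allocation and could not disturb the randomized comparison.

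There is also an internal mismatch: the stated reason for patient blinding does not yet apply at the moment the envelope is opened.

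**Working it through.** The point concerns sequence, so the main check is to put the stated steps in order and ask of each whether it depends on the arm.

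1. **Arrival:** envelope opened. The patient is normally awake, since induction follows and the preoperative section says sedatives are not routine.
2. **Standard monitoring, venous access, induction and intubation:** one description for all patients. Arm not needed.
3. **Arterial catheter, the source of PPV:** after induction, in every patient. The side is set by the lesion, not by the arm of the trial.
4. **Central venous catheter, the source of CVP:** in every patient.
5. **Scalp block, head holder, urinary catheter, park bench position, re-check of lines:** no distinction by arm.
6. **Activation of the fluid protocol, during surgery:** the first step that needs the arm.

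The exact moment of activation is presumably in Fig 3, which is not shown. That does not affect the conclusion. Neither index can be read before its catheter is in, and the arterial catheter is placed after induction. Whatever Fig 3 says, the reveal precedes the earliest possible use of the arm by at least induction and line placement.

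**Does the stated reason for unblinding cover steps 1 to 5?** The article's reason is that fluid must be given by protocol. Before step 6 there is no arm-specific protocol fluid to give; the only fluid rule stated for all patients is weight-based maintenance. So the reason covers step 6 onward only.

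**Size of the fluid effect.** The document gives no volume for the set-up period and nothing on how it might differ by arm. Any figure would be an assumption divided by the target difference, so none is offered.

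**Room for losses.** This is the one related figure that can be reproduced.

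- Inputs from Sample size calculation: 25 per group, 80% power, two-sided 0.05, 5% dropout, 54 in total.
- Dropout step: 25 / (1 − 0.05) = 26.3, rounded up to 27 per group, or 54. This agrees with the plan.
- No SD is stated. Setting power to exactly 80% at 25 per group gives a standardized difference of (1.960 + 0.842) / √(25/2) = 0.792.
- Power at n per group = Φ(0.792 × √(n/2) − 1.960):

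| n per group | Power |
|---|---|
| 27 | 82.9% |
| 25 | 80.0% |
| 23 | 76.6% |

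The allowance therefore covers two losses per group from any cause. This shows only that there is little slack. The document does not say that set-up failures would be removed.

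**The case against.** The case against has real force on several points.

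- **A reader might infer that early fluid does enter the comparison.** The text does not establish this. The outcome definition would allow it, but the model uses t2 to t5, and a window starting at t2 may begin after set-up. The schedule is in Fig 1, which is not shown. The route through the first readings remains open even if t2 is late, but it too is only a possibility.
- **A reader might infer that patients are excluded after allocation because of failed set-up.** No such exclusion is described, and the eligibility criteria read as preoperative. The word modified is not explained, but an analysis plan may define it, so its absence here is not a fault.
- **A reader might infer that allocation concealment is broken.** It is not. Consent is sought the day before surgery, an independent assistant generated the code, and the envelopes are sealed and opaque.
- **Lack of blinding is inherent and disclosed.** This is true from activation onward, and a later opening would not change it. It does not explain the period before activation.
- **Discretion is limited.** Weight-based maintenance for every patient narrows the scope for early differences. The text does not say that it governs all fluid given during set-up.
- **The change may come too late.** Data were to be gathered until 31 May 2025 and the article appeared on 2 June 2025. A six-month extension of approval was foreseen, so recruitment may or may not be closed.

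These objections limit the point to an avoidable exposure. They supply no reason for opening the envelope on arrival.

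**Conclusion.** The rule on when to open the envelope is fixed earlier than the trial needs. It gives the unblinded person who controls the primary outcome knowledge of the arm throughout set-up, and it does not fit the stated basis for patient blinding. The article does not say the patient is told the arm, so this last point is a mismatch of reasoning and not a shown breach.

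The resulting bias is possible, not demonstrated, and the document does not allow it to be sized. The conclusion rests on the described order of steps and on set-up being identical in both arms, both of which are in the text. It does not depend on what Fig 1, Fig 3 or an analysis plan may say about t2 or the modified analysis set. It is worth acting on because the correction costs almost nothing.

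**What to change.** **If patients are still being enrolled:** open the envelope only after both lines are working and the final position has been checked, immediately before the fluid protocol is activated. Count primary-outcome fluid from that point; if t2 already is that point, say so in the text. Analyse all patients whose envelope was opened, as allocated. Failed set-ups then occur before allocation, and plain intention-to-treat loses little.

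**If recruitment has ended:** keep every randomized patient with a recorded volume in the primary analysis, as allocated, and report by arm how many have no recorded volume. State where the outcome window starts, and settle this before the statistician learns which group is which.

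**Cost:** one sentence on procedure and one on analysis. The small downside is that the anesthesiologist learns the arm later, during a busy set-up.
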